### Determination of sample size

Assessments were conducted at three levels, which include community stakeholders, food pantry organization (food pantry, staff/volunteers), and food pantry clients. Convenience samples of community stakeholders, food pantry directors, and food pantry staff/volunteer participants were recruited and included all members of FPCs and all directors, staff/volunteers of the food pantries participating in the study. Sample size was based on the food pantry client expected improvement of 1 in adult food security score from pre-intervention to post-intervention on the food security scale (continuous score from 0 to 10). This unit of change in food security is practically meaningful as it could mean a change in food security level, for example an improvement from very low to low food secure which would indicate a change from not eating enough to an adequate amount of food. Pantry client participants were nested within food pantries. Previous research [22, 23] suggests SD (Y04-Y02) = SD (Y05-Y02) = 2.6 (using the largest conservative estimate) when Y02, Y04, Y05 represent the scores across years and SD represents the standard deviation. Thus, a power analysis was completed where n = the number of paired intervention (trt) and comparison (ctrl) pantries as: Var (estimated trt Y04- Y02 - estimated ctrl Y04-Y02) = 2 * 2.61*2.61/ *n* = 13.6242/n for a total of 224 clients, or 14 participants per pantry. An approximate 30% loss to follow up each year [19] was expected for a total estimate of 40 participants per pantry at baseline to be followed longitudinally throughout the project. An additional 40 new pantry clients were recruited at Y04 and Y05 in order to maintain power to detect a change in food security score in a cross-sectional study design.

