**Methods:**

A longitudinal, matched treatment and comparison study was conducted in 24 rural, high poverty counties in South Dakota, Indiana, Missouri, Michigan, Nebraska and Ohio. Counties were assigned to a treatment (*n* = 12) or comparison (n = 12) group. Intervention activities focus on three key components that impact food security: 1) community coaching by Extension Educators/field staff, 2) FPC development, and 3) development of a *MyChoice* food pantry. Community coaching was only provided to intervention counties. Evaluation components focus on three levels of the intervention: 1) Community (FPCs), 2) Food Pantry Organization, and 3) Pantry Client & Families. Participants in this study were community stakeholders, food pantry directors, staff/volunteers and food pantry clients. Pantry food access/availability including pantry food quality and quantity, household food security and pantry client dietary intake are dependent variables.

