## Methods/design

### Study design

*Voices for Food* used a longitudinal matched intervention and comparison design. Two matched treatment and comparison communities per state (*n* = 24) were selected to participate in the study based upon community and food pantry attributes. Institutional Review Board approval was obtained for this study prior to all intervention activities.

*Voices for Food* utilized the *Voices for Food Model of Behavior Change* (Fig. 1) to guide implementation activities. To address the hypotheses, *Voices for Food* focused on two key components that work together to impact food security in selected treatment communities: 1) Community coaching by Extension Educators/field staff, 2) provision of *Voices for Food* materials that describe, a) FPC development and/or support, and b) the transition to a *MyChoice* food pantry. In comparison communities, *Voices for Food* activities focused on one component: the provision of a *Voices for Food* materials that describes, a) FPC development and/or support, and b) development of a *MyChoice* food pantry*.* The notable difference between the treatment and comparison communities is that comparison communities did not receive coaching from a community coach throughout the implementation of Voices for Food. All participants in both treatment and comparison groups were blinded to the intervention. There were no circumstances in which unblinding was permissible.

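### The sample-size variance has no between-pantry term although counties are assigned, n is mislabelled as pantry pairs, and the stated 224 clients at 14 per pantry fit 16 pantries, not 24

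*Protocol article*

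**What the plan says.** The Abstract (Methods) describes a study "conducted in 24 rural, high poverty counties", 12 treatment and 12 comparison, and says that "Counties were assigned to a treatment" or comparison group. Study design confirms the count: "Two matched treatment and comparison communities per state", over six states, hence 24 communities or 12 pairs.

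Determination of sample size sets the target as an "expected improvement of 1 in adult food security score from pre-intervention to post-intervention" on a 0 to 10 scale. It states that "Pantry client participants were nested within food pantries". It takes "SD (Y04-Y02) = SD (Y05-Y02) = 2.6 (using the largest conservative estimate"), defines "n = the number of paired intervention (trt) and comparison (ctrl) pantries", and writes the variance of the difference in change as 2 × 2.61 × 2.61/n, that is "13.6242/n for a total of 224 clients, or 14 participants per pantry". It then allows for roughly 30% loss per year and arrives at 40 clients per pantry at baseline. No alpha, power, ICC, between-pantry variance or design effect appears.

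**The concern.** The text acknowledges nesting and then uses a variance built only from the SD of one client's change score. When whole counties are assigned, any variation between pantries in mean change adds to the variance of the treatment contrast, and adding clients within pantries does not remove it. The formula therefore understates the variance for any positive ICC of change.

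Two further faults sit in the same paragraph. The definition of n does not match the answer drawn from it, and the total and the per-pantry number do not multiply out to the number of pantries in the study. Food security is the outcome on which the study was sized. A reader who takes 224 as adequate for a 1-point difference could read too much into a null result.

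**Working it through.** **Inputs from the protocol.** SD of change 2.61 (the formula; the text gives 2.6); difference 1 point; 224 clients; 14 per pantry; 24 communities, 12 per arm; 30% loss per year; 40 per pantry at baseline.

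**Assumed, because not stated.** Two-sided 5%; 80% as the reference power; ICC of change from 0 to 0.10.

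**1. The plan's own figures.** 2 × 2.61² = 13.6242, as stated. For independent clients, a normal test and 80% power, n per arm = 13.6242 × (1.960 + 0.842)² = 106.9, so 107 per arm or 214 in all. The stated 224 is 112 per arm: variance 13.6242/112 = 0.1216, SE 0.349, power about 82%. It also results from spreading 107 clients over 8 pantries per arm (13.4) and rounding up to 14, since 2 × 8 × 14 = 224. Which route was used cannot be told, because alpha and power are not given. Both are calculations for independent clients.

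**2. The label on n.** With n as 12 pantry pairs, variance = 13.6242/12 = 1.135 and SE = 1.07. That cannot lead to 224 clients. The label is wrong for this formula.

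**3. The count of pantries.** 224/14 = 16. The study has 24, and 24 × 14 = 336.

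**4. Variance with clustering.** With m clients followed up per pantry and k pantries per arm,

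Var = 2 × 2.61² × [1 + (m − 1) × ICC]/(k × m),

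tested with t on 2k − 2 df, or k − 1 df if analysed as pairs. Example for m = 14, k = 12, ICC 0.05: design effect 1 + 13 × 0.05 = 1.65; Var = 13.6242 × 1.65/168 = 0.1338; SE = 0.366; power 74% on 22 df.

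| ICC (assumed) | Design effect | 16 pantries of 14 (224), 14 df: SE, power | 24 pantries of 14 (336), 22 df: SE, power |
|---|---|---|---|
| 0 | 1.00 | 0.349, 76% | 0.285, 92% |
| 0.02 | 1.26 | 0.392, 66% | 0.320, 85% |
| 0.05 | 1.65 | 0.448, 55% | 0.366, 74% |
| 0.10 | 2.30 | 0.529, 42% | 0.432, 60% |

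The drop from 82% to 76% at ICC 0 comes only from using 14 df in place of a normal test.

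**5. Where 80% is lost.** With 14 in all 24 pantries, power stays at 80% or more up to an ICC of about 0.033 on 22 df, or about 0.023 on 11 df for 12 pairs.

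**6. Minimum detectable difference** at m = 14, k = 12, 80% power, 22 df: about 0.89 at ICC 0.01, 1.07 at 0.05 and 1.27 at 0.10.

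**7. Attrition.** 40 × 0.7³ = 13.7, so 40 at baseline returns about 14 after three annual losses. The baseline number covers dropout to the last time point and leaves no margin for clustering.

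**The case against.** The strongest reply is that the trial as laid out is larger than its stated total. If 14 clients are retained in all 24 pantries, there are 336, and 80% power survives a small ICC. This stands. A reader might infer that the size is adequate only if the ICC is exactly zero and degrees of freedom are unlimited; the 24-pantry figures show that this is not so. A reader might also spread the 224 over 24 pantries, about 9 each, but the protocol plans 14 per pantry, so that layout should not be used to measure the loss.

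The variance is written for the change from Y02 to Y04. After two annual losses 40 × 0.7² = 19.6 clients per pantry would remain, and power on 22 df would be about 92% at ICC 0.02, 81.5% at 0.05 and 65% at 0.10. This also stands, but the target effect is pre- to post-intervention, and by Y05 the number is back to about 14.

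Reading n literally as 12 pairs gives about 15% power. A reader might take that as the trial's real power. It is not: it combines a client-level SD with a count of pantries, and it shows only that the label is wrong.

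The mixed-model regression under Statistical analysis may account for clustering, and its random effects can be left to a fuller plan. That protects the analysis but does not change what the stated size was computed from. Matching may recover some between-county variance; the formula takes no credit for it, and an analysis by pairs has 11 df. The additional clients recruited at Y04 and Y05 serve a cross-sectional comparison, and their contribution to the longitudinal contrast cannot be worked out from the article.

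**Conclusion.** The point holds. The stated variance omits the clustering that the same paragraph describes, n is mislabelled, and 224 at 14 per pantry does not fit 24 pantries. These three faults do not depend on any assumption about alpha, power or ICC.

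The size of the shortfall does depend on them. Under a two-sided 5% test, SD 2.61 and a 1-point difference, the stated 224 falls below 80% power on cluster-level df even at ICC 0 (76%), and to 42% at ICC 0.10. With 336 clients in 24 pantries the size is adequate up to an ICC of about 0.033 (0.023 on 11 df) and short above it. The protocol gives no ICC, so it does not support the stronger conclusion that the trial as conducted is underpowered.

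**What to change.** Rewrite the sample-size paragraph:

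- State the variance as 2 × 2.61² × [1 + (m − 1) × ICC]/(k × m), with m clients followed up per pantry and k pantries per arm, and drop the definition of n as pantry pairs.
- Reconcile the total of 224 and the 14 per pantry with the 24 pantries.
- State alpha and power, and use t critical values on cluster-level df (22, or 11 if the 12 pairs are analysed as pairs).
- Give power or the minimum detectable difference at m = 14, k = 12 over an ICC range labelled as assumed, for example 0.01 to 0.10.

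The cost is one paragraph and a small table. No extra recruitment is needed, and Study status has data collection ending in November 2017. The downside is a less favourable stated figure: at 80% power on 22 df the detectable difference exceeds 1 point once the ICC passes about 0.033.

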### Matching intervention and comparison communities

Prior to recruitment, intervention and comparison communities were matched based upon the criteria for identifying communities and the characteristics of the local food pantry in the community. Pantry characteristics that aided in matching communities were: physical location, distance to another potential pantry, administering organization, hours and days of operation, level of client-choice, interest in study participation and working with Cooperative Extension, number of households served, an estimate of long-term pantry users (greater than 2 years), pounds of food distributed per month, government commodity program assistance (e.g. The Emergency Food Assistance Program [TEFAP], Food Distribution Program on Indian Reservations [FDPIR], and Commodity Supplemental Food Program [CSFP], food bank partnership, infrastructure and capacity (storage, shelving, etc.), and predominant racial/ethnic group served at the pantry.

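### The required size is given as 224 clients or 14 per pantry, but the two agree only for 16 pantries and the design has 24

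*Protocol article*

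**What the plan says.** The Methods part of the abstract fixes the number of clusters: "Counties were assigned to a treatment (*n* = 12) or comparison (n = 12) group". The Study design section agrees: "Two matched treatment and comparison communities per state (*n* = 24) were selected to participate in the study", which is two treatment and two comparison communities in each of six states. Matching used "the characteristics of the local food pantry in the community", and the Community champion section likewise speaks of a single participating pantry. One pantry per community, 24 in all, is therefore the natural reading, although it is never written as a count.

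The Determination of sample size section powers the study on an "expected improvement of 1 in adult food security score from pre-intervention to post-intervention", with "SD (Y04-Y02) = SD (Y05-Y02) = 2.6 (using the largest conservative estimate") for the change. It defines n as the number of treatment and comparison pantry pairs and gives the variance of the difference in change as 2 × 2.61 × 2.61/n = 13.6242/n. From this it concludes "for a total of 224 clients, or 14 participants per pantry". It then expects about 30% loss each year and arrives at "40 participants per pantry at baseline to be followed longitudinally throughout the project". Alpha, sidedness, power and an intracluster correlation (ICC) are not stated in the article.

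**The concern.** The total and the per-pantry figure are presented as one requirement in two forms, and they should convert into each other through the number of pantries. With 24 pantries they do not.

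This is the article's only sample size justification, and it rests on client food security. The Discussion names retention of a transient population as a main challenge, so the analysable number is the figure readers will check. If, say, 250 clients had paired data at Y05, the trial would meet one stated target and miss the other. The formula cannot settle which one holds, because its n is defined as pantry pairs, and under that definition it gives neither figure.

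**Working it through.** **Inputs.** 24 pantries, 12 per arm (abstract and Study design, one pantry per community). Difference 1 point, SD of change 2.61, loss about 30% a year (Determination of sample size). Follow-up from Y02 to Y05, three yearly intervals (Organization/scheduling data collection). Assumed, because the article does not state them: two-sided 5% test, 80% power, normal approximation.

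**1. The variance constant.** 2 × 2.61² = 13.6242, as printed.

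**2. Does the formula give 224?** With n as clients per arm, n = (1.960 + 0.842)² × 13.6242/1² = 106.9, so 107 per arm and 214 in total (108 and 216 with the t distribution). Other choices, over SD 2.6 and 2.61, do not give 224 directly either:

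| Test | 80% power | 85% power | 90% power |
|---|---|---|---|
| One-sided 5% | 168–170 | 196 | 232–234 |
| Two-sided 5% | 214 | 244–246 | 286–288 |

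Rounding up to whole clients per pantry does give it, but only for 8 pantries per arm:

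- 8 per arm: 107/8 = 13.4, rounded up to 14; 14 × 16 = 224.
- 12 per arm: 107/12 = 8.9, rounded up to 9; 9 × 24 = 216.

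**3. The mismatch.** 224/14 = 16 pantries. For 24 pantries, 14 × 24 = 336 and 224/24 = 9.33 per pantry; 336/224 = 1.5.

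**4. The definition of n.** With n = 12 pairs, the variance is 13.6242/12 = 1.135 and the standard error 1.07. Power for a 1-point difference is then about 15%. The formula leads to about 107 only if n counts clients per arm.

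**5. The baseline target.** Three yearly losses leave 0.7³ = 0.343.

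- From 14 per pantry: 14/0.343 = 40.8, which fits the stated 40. Two losses would give 14/0.49 = 28.6, so three is the number that reproduces it.
- From 9.33 per pantry: 9.33/0.343 = 27.2, so about 27 to 28.
- Forward: 40 × 0.343 = 13.7 per pantry; 24 × 40 = 960, and 960 × 0.343 = 329 clients.

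**6. Power at each total.** With standard error √(13.6242/n) and n clients per arm:

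- 336 in total, n = 168: standard error 0.285, power 94%.
- 224 in total, n = 112: standard error 0.349, power 82%.

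**7. Sensitivity to nesting.** The section says that clients are nested in pantries, but the variance has no term for it. Taking a design effect of 1 + (m − 1) × ICC, with m clients per pantry in 24 pantries and an assumed ICC of 0.01 to 0.05:

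- m = 14: design effect 1.13 to 1.65, power 91% to 78%.
- m = 9.33: design effect 1.08 to 1.42, power 79% to 67%.

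**The case against.** The best defence is that the figures used in the field agree with each other. Fourteen analysable clients per pantry and 40 at baseline are linked by the stated yearly loss, and only the total of 224 is out of line. Recruiting 40 in each of 24 pantries would leave about 329 clients, well above 224 and about 2% below 336. Data collection was planned to end in November 2017, and no analysis depends on the sentence. All of this stands. It limits the consequence but does not reconcile the two figures.

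Three stronger readings are tempting, and the article does not support them.

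- A reader might infer that the baseline 40 is wrong. It is not shown to be: it follows from 14, and is only larger than needed if 224 is the true requirement. The three losses are inferred from the Y02 to Y05 schedule, as the article does not write them out.
- A reader might infer that the trial was planned too small. The mismatch alone does not show that, given the 329 expected to remain.
- A reader might take 224 as the requirement without clustering and the extra 112 as an allowance for clustering. The article gives no ICC, design effect or allowance, and under the assumptions above the formula gives 214, not 224.

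The clients newly recruited at Y04 and Y05 do not close the gap either. They have no Y02 score, and the calculation is built on change from Y02.

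**Conclusion.** The sentence is wrong as written for this design: 224 in total and 14 per pantry describe 16 pantries, and the article describes 24. The two implied targets are 336 and 224, a 50% difference, and nothing in the article says which was meant. This part needs no assumption beyond one pantry per community; more than one would widen the gap. The definition of n as pantry pairs is also wrong for the result drawn from it.

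The exact recovery of 224 with 8 pantries per arm suggests a calculation made for 16 pantries and not updated. That is an inference and depends on the assumed 5% and 80%. The powers of 94% and 82% likewise rest on an assumed two-sided 5% test, on n as clients per arm and on no clustering. The ranges under clustering rest on assumed ICCs.

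**What to change.** Rewrite the sentence so that the total, per-pantry and baseline figures agree for 24 pantries. If 14 per pantry and 40 at baseline stand, the total is 336, or 168 per arm. If 224 is the requirement, the per-pantry figure is 9.3 (10 when rounded up to whole clients), and the text should say that 40 at baseline exceeds what is needed.

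Define n as clients per arm, if that is how it was used. State the number of pantries, alpha, sidedness and power that entered the calculation, and write out the three yearly losses behind the 40. Say whether clustering was allowed for, and do not present the difference between 224 and 336 as such an allowance unless one was actually calculated.

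The cost is a correction of wording and arithmetic. Recruitment does not change.

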### Participant recruitment

Community stakeholders, pantry directors, pantry staff/volunteers, and pantry clients were recruited to participate in this study. All participants were enrolled using the IRB-approved consent process. Community stakeholders were recruited for survey completion during the first FPC meeting after the intervention started, as they joined the council and at each data collection time point. If a FPC had not formed, community stakeholders were recruited from the community. Food pantry directors were recruited to complete surveys and were identified by the coach. Food pantry staff/volunteers were identified by pantry directors and were recruited for survey completion at each data collection time point. All food pantry staff/volunteers, directors and community stakeholders received $10 gift cards to local grocery stores when possible at each data collection time point for completing surveys.

Pantry client participants were recruited with fliers posted throughout the community, in high-traffic areas within the pantry, and by word-of-mouth. On the day of data collection, food pantry clients were screened for eligibility to ensure they were legal adults, could read and speak English, had visited the pantry more than once in the last 12 months, had access to a computer or telephone to complete follow up assessments, and desired to participate in the study. Food pantry clients were eligible to receive $30 total in stipends to a local grocery store at each data collection time point if all surveys were completed.

### Assessment tool descriptions

Eleven assessment tools were used to evaluate the effectiveness of the intervention as a whole. All questionnaires were pilot tested for feasibility prior to collecting pre-intervention data. Where possible, the project team used previously validated assessment tools or questions. All assessments were completed at pre-, mid- and post-intervention unless otherwise indicated. Table 1 summarizes the assessment tools and data collection schedule.

**Table 1 Tab1:** Description of Assessment Tools

	Pre	Mid	Post	Subject
Community Level				
Community Stakeholders Survey	X	X	X	Project Staff
Food Council Implementation Tracking Form	X	X	X	Community Champion
Training Tracking Form	Ongoing			Pantry Director Community Champion
Food Pantry Organization Level				
Food Pantry Director Survey	X	X	X	Project Staff
Food Pantry Staff/Volunteer Survey	X	X	X	Project Staff
Food Pantry Inventory Log	X	X	X	Project Staff
Food Pantry MyChoice Observation Tool	X	X	X	Project Staff
Food Pantry Client Level				
Food Pantry Client Survey	X	X	X	Project Staff
ASA24® Dietary Recall	X	X	X	Project Staff
Participant Food Box Content Log	X	X	X	Project Staff

### Community-level assessment tools

#### Community stakeholders survey

A 23-question *Community Stakeholders Survey* assessed community stakeholder perceptions in participating communities. This survey collected demographic information, perceptions of food security in the community, past experience with FPCs or similar organizations and feedback on the *Voices for Food: Food Council Guide*, and experience with the community coach.

#### Food council implementation tracking form

A three-part *Food Council Implementation Tracking Form* tracked changes occurring in the FPC including: activities and accomplishments. Additionally, FPCs will provide key documents developed during the intervention, including meeting agendas, meeting minutes, press releases, organizational charts, mission/vision statements and strategic plans to the research team.

